## Study procedures

### Physical activity

Physical activity will be monitored by an objective physical activity monitoring through the intervention (Polar Active). Additionally, leisure time physical activity during the intervention period will be assessed by the modified Minnesota Leisure-Time Physical Activity Questionnaire (Taylor et al., 1978). The modified version to be used in the present study has not been formally validated while the original questionnaire has been validated (Bonnefoy et al., 2001). The modified version of the questionnaire is translated into Dutch from the modified Finnish questionnaire which feasibility has been, however, confirmed at the large-scale 4-year lifestyle intervention study (DR’s EXTRA) (Hakola et al., 2015). All ergospirometry tests and HI sessions will be executed in an allocated Cardio fitness program.

### Dietary intake

The subjects will get instructions to keep their diet unchanged. Online dietary intake lists will be taken as previously described (voedingscentrum.nl). Online 4-day dietary lists are taken just before the intervention period at baseline, and 5-day dietary lists are taken midway and at the end of the intervention. The online dietary intake lists will be recorded during predefined consecutive days (3-4 weekdays, 1 weekend day) and checked by researchers.

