**Nature and extent of the burden and risks associated with participation, benefit and group relatedness:**

This study is a continuation of our previous intervention studies aiming to study underlying mechanisms of gut microbiota in liver gene expression in NALFD-NASH subjects (MASH study 2013_207) and our study on the role of microbiota on muscle gene expression and glucose metabolism (APPETITE study 2014_084). Oral microbiota is studied by taking an oral swab of the upper front teeth rime in overnight fasted subjects that refrained from tooth brushing that morning (FATMED study 2016_117). Moreover, we currently are building a large prospective cohort of patients with NAFLD-NASH to follow the natural course of (liver biopsy proven) changes in NAFLD-NASH between baseline and after 5 years (2017_311). Participants will be recruited from our outpatient clinics. An ultrasound or transient electrography will be performed to establish hepatic steatosis, if they do not already have an existing diagnosis. All subjects will in total have six site study visits, and total 21 hours in 12 weeks. At each visit we will collect blood and fecal samples. In addition, body weight will be measured at each visit. Other anthropometrics including height and waist circumference will be screened at baseline. At the baseline (first) and endpoint (final) visit we will collect (ultrasound guided) liver, muscle and subcutaneous adipose tissue biopsies, and Magnetic Resonance Imaging (MRI) and Magnetic Resonance Spectroscopy (MRS) will be performed. During these two visits, bioelectrical impedance will be conducted to screen body composition and resting energy expenditure (REE) will be determined. Also, ergospirometry test will be performed to determine the intensity of the individually prescribed training program and the efficacy of the exercise intervention. Exercise habits will be assessed by a questionnaire for the entire 12-week intervention period. Additionally, an objective physical activity monitoring will be performed through the intervention. Subjects will also fill in online questionnaires regarding their food intake for one week prior to each visit. Glucose monitoring will be conducted for 4 weeks during the intervention, 2 weeks at the baseline and 2 weeks before the end of the intervention to screen the effect of the exercise on glucose metabolism.

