# OBJECTIVES

**Primary Objective:** to evaluate the clinical effect of high-intensity interval exercise on NAFLD liver histology and genes in relation to gut microbiome composition. To do this we will collect:

At baseline and endpoint:

- Anthropometrics (body weight, waist and hip circumference and body composition)
- Ergospirometry tests (VO2max)
- MRI and MRS scan of the abdomen to estimate liver fat content, fibrosis and abdominal fat depot assessed by MR modality, and also the liver fibrosis assessed by transient elastrography (FibroScan)
- Oral swab, Fecal and 24 h urine samples
- Free style Libre glucose monitoring (worn during 2 weeks)
- Blood samples (fasting plasma and DNA)
- (Ultra sound guided) Liver biopsy, muscle and adipose tissue biopsy for histology and gene expression
- REE
- Calf circumference

At mid-intervention:

- Body weight, waist and hip circumference
- Oral and fecal sample
- Blood sample (fasting)

At baseline:

- Height
- Ethnicity

At baseline, mid-intervention and endpoint:

- 4-day dietary intake list before the intervention and 5-day dietary lists before mid-intervention and endpoint

Through the entire intervention

- Physical activity questionnaire
- Objective physical activity monitoring

**Secondary Objective:** to analyse gut microbiota composition and identify novel biomarkers of high-intensity interval exercise effect on NAFLD liver genes progression. Also, we aim to study the relative contribution of each organ (liver/muscle and adipose tissue) in relation to gut microbiota composition and improvement in glucose metabolism upon exercise. To do this we will collect:

At baseline and endpoint:

- Fecal and 24 h urine samples
- Blood samples
- Liver, muscle and adipose tissue biopsy (for histology and gene expression)
- Gut motility

At mid-intervention:

- Fecal samples
- Blood samples

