### Other study parameters (if applicable)

Other study parameters include:

- Body weight will be measured at baseline, mid-intervention and final study visits to include as possible confounding factors.
- Body composition will be measured at baseline and final study visits to include as possible confounding factors.
- Physical activity will be followed by questionnaire.
- REE will be determined at baseline and endpoint.
- Dietary intake lists will be screened before baseline, mid-intervention and final visits to see whether there is changes in dietary habits as possible confounding factor.
- Relative contribution of (RNAseq metabolic pathway based) metabolic changes in each organ (liver/muscle/adipose tissue) and gut microbiota (metabolic pathway) metabolic changes in relation to exercise induced glucose metabolism improvements.
- Calf circumference will be determined at baseline and endpoint.
- Pre- and postexercise blood biomarkers.

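### The diet record lengthens from 4 to 5 days after baseline, so its weekend share falls from 25% to 20% between the time points being compared, and the summary gives a third length

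*Protocol*

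**What the plan says.** Section 6.3.2 (Dietary intake) sets the record length by time point: "Online 4-day dietary lists are taken just before the intervention period at baseline, and 5-day dietary lists are taken midway and at the end". The same section says that the lists are "recorded during predefined consecutive days (3-4 weekdays, 1 weekend day"). Section 2 (Objectives) repeats the lengths: "4-day dietary intake list before the intervention and 5-day dietary lists before mid-intervention and endpoint".

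The summary, in its paragraph on burden and risks, describes something else: "Subjects will also fill in online questionnaires regarding their food intake for one week prior to each visit".

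Section 6.1.3 gives the purpose of the lists: "to see whether there is changes in dietary habits as possible confounding factor". The true change is meant to be nil, since section 6.3.2 also says: "The subjects will get instructions to keep their diet unchanged". Sections 3 and 6.2 show a single intervention group with no randomised comparator.

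**The concern.** The lists serve a before-after comparison, and the instrument changes between before and after. The day added at follow-up is a weekday, so the baseline and follow-up records do not measure the same mix of days. Where people eat differently at weekends, part of any observed change can come from the record and not from the diet.

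A control arm with the same schedule would cancel an artefact of this kind. This study has none. Attribution of liver changes to exercise leans on diet having stayed the same, and the lists are the protocol's direct check of that. A shifted check could suggest a small change that did not occur, or hide a small one that did.

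Separately, three places describe the record and only two of them agree, so site staff and participants cannot tell from the protocol alone how many days are to be recorded.

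**Working it through.** **Inputs from the protocol.** Record length is 4 days at baseline and 5 days midway and at the end (sections 2 and 6.3.2). The mix is 3–4 weekdays and 1 weekend day (section 6.3.2).

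**Step 1: the day mix.** 3 + 1 = 4 and 4 + 1 = 5. No other split of the stated mix gives both lengths, so the plan's own figures are reproduced. The weekend share is 1/4 = 25% at baseline and 1/5 = 20% later. The calendar share is 2/7 = 28.6%.

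**Step 2: the artefact when diet is constant.** Let weekday intake be 1 and weekend intake r, and let daily values be averaged without weights. Both r and the averaging rule are assumptions; the protocol gives neither.

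- Baseline mean: (3 + r)/4
- Later mean: (4 + r)/5
- Difference: (4 + r)/5 − (3 + r)/4 = (16 + 4r − 15 − 5r)/20 = (1 − r)/20 of weekday intake

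**Step 3: size over a range of r.** The last column assumes a weekday intake of 2000 kcal.

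| r (assumed) | Baseline mean | Later mean | Apparent change | kcal/day |
| --- | --- | --- | --- | --- |
| 0.8 | 0.950 | 0.960 | +1.05% | +20 |
| 0.9 | 0.975 | 0.980 | +0.51% | +10 |
| 1.0 | 1.000 | 1.000 | 0 | 0 |
| 1.1 | 1.025 | 1.020 | −0.49% | −10 |
| 1.2 | 1.050 | 1.040 | −0.95% | −20 |
| 1.3 | 1.075 | 1.060 | −1.40% | −30 |
| 1.5 | 1.125 | 1.100 | −2.22% | −50 |

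**Step 4: items concentrated at weekends.** The relative shift grows with r. As an illustration only, an item taken at 5 g on a weekday and 30 g on a weekend day has a baseline mean of (3 × 5 + 30)/4 = 11.25 g and a later mean of (4 × 5 + 30)/5 = 10.00 g. That is −1.25 g/day, or −11%.

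**Step 5: comparison with sampling noise.** Assume independent days, a within-person day-to-day SD of 500 kcal and n = 15. The SD of a 4-day mean minus a 5-day mean is 500 × √(1/4 + 1/5) = 335 kcal, and the standard error of the mean change is 335/√15 = 87 kcal. A shift of 10 to 30 kcal is about 0.1 to 0.3 standard errors. With an SD of 300 kcal the standard error is 52 kcal and the shift is about 0.2 to 0.6 standard errors.

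**Step 6: does the remedy remove it?** With the same mix at every time point, the two means are the same function of r, so the expected artefact is 0 for any r. With 5/7 × weekday mean + 2/7 × weekend mean, both time points estimate (5 + 2r)/7, again with artefact 0. The cost in noise is small. With equal, independent day variances, the variance factor is 25/(49 × 3) + 4/49 = 0.252 against 0.250 for the 4-day list, and 25/(49 × 4) + 4/49 = 0.209 against 0.200 for the 5-day list.

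**The case against.** A reader might infer that an apparent fall in intake is built into the design and that every participant shifts the same way. The documents do not support this. Only the day mix changes by construction. A fall also needs weekend intake above weekday intake and an unweighted mean, and the protocol states neither. Each participant's shift is −1/20 of that person's own weekend-minus-weekday difference, so some may shift upwards and some not at all.

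The case for leaving the plan alone goes further:

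- **Averaging.** How diary days are averaged is normally left to the statistical analysis plan, and weighting by day type would remove the artefact. This stands, and the protocol's silence on weighting is not held against it. The collection schedule, however, is fixed in the protocol, and the mismatch lies there.
- **Size.** The shift in energy is small against sampling noise (step 5). This stands.
- **Role.** The lists are listed among other study parameters, as a check on a possible confounder. Body weight at all three visits and body composition at baseline and end serve the same purpose (section 6.1.3). The mid-to-end comparison uses 5 days both times and is unaffected. All of this stands and limits the importance of the point.
- **Weekend-heavy items.** The documents give no weekend split for any nutrient, and the diet sections do not name alcohol as an output of the lists. Step 4 therefore shows only that the relative shift can be larger for such items; it does not estimate an effect in this trial.
- **The summary.** Its one-week wording might be meant as the window in which the lists are completed. It does not say so, and as written it conflicts with sections 2 and 6.3.2.

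**Conclusion.** The point holds as a minor one. The baseline and follow-up diet records are not like for like: the weekend share falls from 25% to 20% between the time points that are compared, and no control arm would cancel the effect. If daily values are averaged without weights, the comparison can be biased by (1 − r)/20 of weekday intake. For energy this is about −0.5% to −1.4% under an assumed weekend excess of 10% to 30%, zero if weekend and weekday intake are equal, and a small rise if weekend intake is lower. The direction cannot be read from the documents. The bias touches a confounder check; it does not enter any main endpoint. The conflict with the one-week record in the summary rests on no assumption and needs correcting in any case.

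**What to change.** In section 6.3.2, and to match in section 2, specify the same number of days and the same weekday/weekend mix at baseline, mid-intervention and endpoint. Going to 4 + 1 days throughout costs one extra diary day at baseline; going to 3 + 1 throughout costs none. Either removes the artefact whatever r is.

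For lists already collected, compute each participant's intake as 5/7 × weekday mean + 2/7 × weekend mean at each time point. This needs no new data and is slightly noisier, because the single weekend day carries more weight.

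Align the sentence on food intake in the summary with sections 2 and 6.3.2.

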### Anthropometrics

Body weight will be measured at baseline, mid-intervention and final intervention visits. Height will be measured at baseline visit. Circumferences of waist (at the midpoint between the lateral iliac and lowest rib) and hip, thigh will be measured to the nearest 0.5 cm at baseline and endpoint visits. Body mass index (BMI) will be calculated as weight (kg) divided by height (m) squared. Body composition will be determined by bioelectrical impedance in subjects in standing position at baseline and endpoint visits together with ergospirometry test. Also, calf circumference will be measured at baseline and endpoint.

### Cardiorespiratory fitness assessment

To determine the intensity of the individually prescribed training program and the efficacy of the exercise intervention, ergospirometry tests (VO2max) will be carried out on a cycle ergometer at baseline and after 12 weeks together with the department of Cardiology ([name]) and Polifysiek, Hogeschool van Amsterdam. The test will start with a 1-minute sitting period in the saddle followed by a 3-minute warm-up with 0 Watts (W) after that the workload will increase gradually at 6 seconds intervals according to an individualized protocol. The test will be supervised by a physician or another qualified health care professional adequately trained for the task and participants will be verbally encouraged to continue until exhaustion. Respiratory gas exchange and ventilation will be measured by the breath-by-breath method and electrocardiography (ECG) will be recorded throughout the exercise test.

### Resting energy expenditure

REE will be measured at baseline and endpoint visits. Oxygen consumption and CO_2_ production will be measured for 20 minutes using a ventilated hood system. With these measurements the REE and respiratory quotient (RQ) can be calculated. The RQ represents the ratio of CO_2_ exhaled to the amount of oxygen consumed by the individual and represents whole body substrate oxidation (glucose, fat, and protein oxidation). The abbreviated Weir equation is used to calculate the 24-hour energy expenditure.

### Blood pressure and heart rate

Blood pressure and heart rate will be measured at baseline and final intervention visits.

### Magnetic Resonance Imaging

MRI scans of the abdomen area will be performed to estimate liver fat content, fibrosis, visceral and subcutaneous fat and quantitate gut motility on the 3T Philips Ingenia MRI scanner. Altogether the scans to estimate abdominal adipose tissue depot, hepatic fat and fibrosis and gut motility will take approximately 60 minutes.

### Magnetic Resonance Spectroscopy

The intrahepatic content of lipid (IHCL) will be quantified through MRS.

### Liver Transient Elastrography

Transient Elastrography, also referred to as FibroScan, will be performed to screen and identify the patients who do not have a previous diagnosis of NAFLD. FibroScan will be performed at the screening visit and also at the endpoint after the intervention period. Recommended values for different stage of fibrosis are described in Table 2.

Table 2. Recommended values for fibrosis staging**.**

|  | F0-F1(kPa) | F2 (kPa) | F3 (kPa) | F4 (kPa) |
| --- | --- | --- | --- | --- |
| NAFLD/NASH (liver stiffness) | ≤7.0 | ≥7.5 | ≤10 | ≥14.0 |

KPa, kilopascals; NAFLD, non-alcoholic fatty liver disease; NASH, non-alcoholic steatohepatitis

### Urine and microbiota samples

Stool and oral microbiota samples will be collected at baseline, midterm, and endpoint visits to determine changes in microbiota composition upon the high intensity exercise intervention. The oral samples will be taken by collecting a swab of the upper tooth rim of the front teeth in overnight fasted subjects that refrained from tooth brushing that morning. Moreover, collection on feces collection system by the subject him/herself. It is then transported to AMC on ice packs, and there it will be frozen at -80°C until analysis. The analysis will be done by sequencing at Novogene. 24-hour urine collection will be performed for at baseline and endpoint of the intervention to determine metabolite content. The samples are collected by the patient him/herself and frozen at -80°C until analysis.

### Blood samples

For determination of various biomarkers and metabolomics, total of 3 x 60 ml of venous blood samples will be withdrawn in overnight fasted state. Stated volume of venous blood includes the spare blood samples as well. Also, blood samples will be taken after the first and last exercise session for pre- and postexercise biomarkers.

### Glucose monitoring

Glucose monitoring (Freestyle Libre) will be performed at weeks at the baseline, and at weeks 11 and 12 before the end of the intervention. Altogether 4 weeks of glucose monitoring during the intervention. The subjects are instructed to perform 8-10 scans per day. After the 2-week monitoring period the results will be processed by a specific software in order to get an estimate of the daily fluctuation of blood glucose concentration.

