# TREATMENTS OF SUBJECTS

## Treatment

The intervention group will follow a high-intensity interval training (HI) protocol on a cycle ergometer (Hallsworth et al., 2015). To determine the intensity of the individually prescribed training program and the efficacy of the exercise intervention, ergospirometry tests will be performed in collaboration with the department of Cardiology AMC ([name]) that has all expertise to execute this study. The training sessions and ergospirometry tests will be carried out in Polifysiek, Hogeschool van Amsterdam. Furthermore, physical activity of study subjects will be monitored through the intervention by questionnaires. These are described later in the chapter of study procedures. Subjects are asked to keep their diet and weight unchanged.

The exercise intervention will start immediately after the ergospirometry test. In detail, the concept of HI involves repeated bouts of exercise at an intensity of 85 % of W_max4_ interspersed by recovery periods based on a baseline ergospirometry test. W_max4_ refers to the hypothetical workload sustainable for 4 min (Tornvall G, 1963). While being hypothetical, W_max4_ is useful for defining the presumably optimal intensity for work intervals at HI. The intervention group will perform HI session involving 5 bouts of 2-4 minutes work intervals (at 85 % of W_max4_) interspersed by 3 minutes of active recovery (at 10 % of W_max4_) period twice per week on non-consecutive days for 12 weeks. Each work interval will be 2 minutes long in the first week with 5 seconds added per each exercise session (i.e. 10 seconds per week) so that HI intervals will be 4 minutes long by week 12. If the subject fails to complete the work interval, he/she will still be instructed to continue the exercise session by starting the following scheduled work interval(s) after the recovery period(s). At the beginning of the intervention period, each HI session will last approximately 40 minutes, including warm-up (at 30% of W_max4_), recovery periods and cool-down (at 20 % of W_max4_). At the end of the intervention period, each HI session will last approximately 50 minutes. HI will be conducted in a group of 1-3 subjects closely supervised by exercise physiologist, or some other qualified health care professional (e.g. biomedical laboratory scientist) adequately trained for the task.

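### The protocol does not ensure that the two-week baseline glucose recording ends before training starts, although it is the only reference for the glucose change

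*Protocol*

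**What the plan says.** Section 6.3.12 (Glucose monitoring) says that recording "will be performed at weeks at the baseline, and at weeks 11 and 12 before the end of the intervention". The second period has week numbers and the first has none. The section then gives the total: "Altogether 4 weeks of glucose monitoring during the intervention".

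The Summary, under burden and risks, repeats this: "Glucose monitoring will be conducted for 4 weeks during the intervention, 2 weeks at the baseline and 2 weeks before the end of the intervention". It gives the purpose as "to screen the effect of the exercise on glucose metabolism". The same paragraph places the ergospirometry test at the baseline and final visits.

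Section 5.1 (Treatment) fixes when exercise begins: "The exercise intervention will start immediately after the ergospirometry test". Supervised sessions are held "twice per week on non-consecutive days for 12 weeks", and Table 1 adds 140 minutes of home exercise per week in the first block.

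Other sections point towards a baseline that precedes training:
- Section 2 (Objectives) lists a two-week sensor wear among the baseline and endpoint measurements, next to the biopsies, imaging and VO2max.
- Figure 1 prints week 0 with a window of plus or minus 3 weeks.
- Section 6.3.2 (Dietary intake) uses baseline for food records made just before the intervention period.

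No section says whether the first sensor must be finished before the first session. Section 6.2 marks randomisation as not applicable, so there is no control group.

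**The concern.** With one arm, the effect of exercise on glucose can only be read as a within-person change from a period without the training programme to a period near its end. Two sections place the reference period inside the intervention, and a third starts training straight after a baseline test. An investigator who follows those three could fit the first sensor at the baseline visit and record the first two training weeks. One who follows the Objectives list and the figure could finish the recording beforehand. In a first stage of 15 subjects, the degree of overlap could even differ between people.

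A reference period that already contains training may hide part of the effect, and this cannot be repaired after the data are collected. The glucose change also feeds the analysis of how much liver, muscle and adipose tissue contribute to improved glucose metabolism, which is part of the secondary objective. Sensor-based glucose is named in the Summary's main study parameters as well.

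**Working it through.** **1. The stated total.** The inputs are 2 weeks at baseline and 2 weeks at weeks 11 and 12 (Summary and section 6.3.12).

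2 + 2 = 4 weeks, which reproduces the protocol's figure. All four weeks fall during the intervention only if the baseline fortnight is counted in it. If the first recording ended before training, the total would still be 4 weeks, but only 2 of them would be intervention weeks.

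**2. What full overlap would contain.**
- Supervised sessions: 2 per week × 2 weeks = 4, out of 2 × 12 = 24 (section 5.1).
- Home exercise: 140 min/week × 2 weeks = 280 min (Table 1).

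**3. How much of the change could be lost.** The protocol gives no glucose effect size, SD or time course, so the time courses below are assumptions. Let f(t) be the effect after t weeks of training. Let M1 be its mean over weeks 0 to 2 and M2 its mean over weeks 10 to 12, that is, study weeks 11 and 12. Against a pre-training reference the expected change is M2. Against a fully overlapping reference it is M2 − M1. The lost share is M1 / M2.

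*Linear*, f(t) = t/12: M1 = 1/12 and M2 = 11/12, so the lost share is 1/11 = 9.1%.

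*Exponential with half-time h*, f(t) = 1 − exp(−kt), k = ln 2 / h. The mean over weeks a to b is 1 − [exp(−ka) − exp(−kb)] / [k(b − a)].

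| Half-time | M1 | M2 | Lost share |
|---|---|---|---|
| 4 weeks | 0.155 | 0.851 | 18% |
| 2 weeks | 0.279 | 0.977 | 29% |
| 1 week | 0.459 | 0.999 | 46% |

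*Limits with full overlap.* If there is no effect in the first two weeks, M1 = 0 and the loss is 0%. If the effect is immediate and constant, as for a purely acute response to each session, M1 = M2 and the loss is 100%. The second limit is an upper bound. Table 1 lengthens the work intervals from 120-160 s to 200-240 s and reduces home exercise from 140 to 100 min/week between the first and last blocks, so the stimulus is not the same in the two periods.

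*Half overlap* (one week before training, one week after its start). For the linear case M1 = 0.5 × (0.5/12) = 0.0208, and 0.0208 / 0.9167 = 2%. For the immediate case the loss is 50%.

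*No overlap.* The loss is 0% for every time course.

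**The case against.** The strongest reply is that this is loose wording and that a pre-training recording was meant throughout. Several points support it:
- Both passages that give the four-week total themselves call the first period baseline.
- The caption of Figure 1 describes all procedures as performed during the 12-week intervention. These include the baseline ergospirometry test, which section 5.1 places before exercise. The protocol's use of the phrase is therefore not strict.
- Fourteen days of wear fit inside a week-0 window of plus or minus 3 weeks.
- Nothing ties the fitting of the sensor to the ergospirometry visit.
- The sentence in section 6.3.12 that should place the first period is garbled.

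These points have force. A reader might infer that the study has no exercise-free glucose reference and that its glucose result is biased towards no change. The documents do not support that. Overlap is possible but not prescribed, and attenuation also requires an early effect in the same direction as the late one, on which the protocol gives no data.

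The objection does not remove the gap. A plus-or-minus window permits a late sensor as well as an early one. The Objectives list allows a pre-training recording without requiring it. The only statements that relate the recording to the intervention, made in two separate places, put it inside.

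It is also fair to say that the reach is limited. Sections 6.1.1 and 6.1.2 do not list glucose as a main or secondary endpoint, section 6.1.3 places the organ-contribution analysis among other parameters, and the sample size in section 4.4 does not depend on it.

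**Conclusion.** The point holds as an unresolved contradiction about timing. The protocol does not secure an exercise-free glucose reference, and in a single-arm study that reference is the only comparator. Whether any bias arises depends on how the sensor is actually scheduled.

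If the first recording fully overlaps training weeks 1-2, the loss ranges from nil to nearly the whole effect, with 9% for linear build-up and 18% to 46% for half-times of 4 to 1 weeks as intermediate cases. These figures show sensitivity to assumed time courses and are not estimates for this trial. The consequence is confined to the glucose comparison and the organ-contribution analysis that uses it. The histology, gene-expression and microbiota endpoints are unaffected.

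**What to change.** Reconcile the Summary (burden and risks), section 2, Figure 1, section 5.1 and section 6.3.12 on one sequence:
- State that the first 14-day sensor recording is completed before the first training session. It could be fitted at screening or early in the week-0 window.
- Give that period explicit timing in section 6.3.12, as is already done for weeks 11 and 12.
- Correct the four-week total in both places to two weeks before the intervention and two weeks at its end.

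No extra recording period or additional subject is needed. The cost is fitting the sensor about two weeks earlier, with a possible short delay to the first session. How this fits the six planned visits should be checked. If the sensor is fitted before eligibility is confirmed, an occasional one will be spent on a person who is not enrolled.
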